### Process data

Process data will be compiled using a range of sources to determine the quality and intensity of intervention delivery. These include (1) CBR worker ‘sub-district’ logbooks, including type and number of community engagement tasks completed, (2) CBR worker ‘participant’ logbooks including home visit forms (modules undertaken, duration and travel time) and assessment forms, (3) monthly observation of CBR visits by supervisor and completion of the ENACT (Enhancing Assessment of Common Therapeutic factors) rating scale [56] adapted and validated for the Ethiopian context. The adapted ENACT assesses communication skills, engagement with the individual, family and community, assessment of medication adherence, physical health, substance use and suicide risk assessment, (4) observation of CBR home visits by an external clinician (psychiatric nurse or psychiatrist) to complete the ENACT, providing an independent assessment of CBR worker skills, (5) CBR worker competency assessment by supervisor (rating of 1 to 3 given for each of 47 CBR competencies, e.g. ability to conduct community awareness raising meeting), (6) CBR worker self-assessed competency form, (7) supervisor logbook including number of supervision sessions attended, (8) health centre records to determine frequency of contact with participant, and (9) participant-reported structured assessment of the extent to which CBR met their needs.

### Qualitative

In-depth interviews (IDIs) will be conducted at baseline and 12 months with a sub-sample of patients and caregivers to gather information on the impact of CBR and other factors on the experience of illness and recovery. Around eight to ten participant dyads from each treatment arm will be included depending on when theoretical saturation is reached. After gaining separate informed consent, interviews will be audio-taped, transcribed in Amharic and then translated into English prior to conducting a thematic analysis. IDIs will be conducted with four to eight community leaders to understand their role in CBR and their perception of its potential impact. IDIs and FGDs will be conducted with CBR workers and supervisors to understand their experience of delivering CBR and its perceived impact on participants. One or two focus groups will also be held with health centre nurses to understand their experience of working with CBR workers.

### Power calculation

We estimate that 182 participant dyads (mean 3.4 participants/sub-district) will be available for recruitment. Assuming that there is 23 % attrition, the final sample size for analysis will be 140 participant dyads in 54 sub-districts (mean 2.6 participants/sub-district). This sample size will allow us to detect a 20 % absolute difference in WHODAS 2.0 scores between treatment arms with 85 % power and 5 % significance, assuming a *k* (coefficient of variation) of 0.14 and a within-cluster standard deviation (SD) of 16. The value of *k* was extracted from symptom severity data by sub-district from an RCT in Butajira evaluating trimethoprim as an adjuvant treatment for schizophrenia (*k* = 0.11) [57]. A more conservative estimate of *k* has been used to account for the potential therapist effect; each CBR worker will cover around three sub-districts and CBR intensity and quality may differ by CBR worker. The mean WHODAS 2.0 in intervention and control arms and within-cluster SD were derived from an Indian study of people with schizophrenia [58].

The estimate of 182 participant dyads available for recruitment was arrived at using (1) the total adult population of Sodo district, (2) the local prevalence of schizophrenia (0.05 %) [59], (3) an estimate that 60 % of cases will be detected and agree to participate in the PRIME cohort, (4) an assumption that 70 % of cases will be eligible for RISE, based rates of continuous illness found in a previous study in the neighbouring district of Butajira [5], and (5) an assumption that approximately 80 % of eligible cases will agree to participate, based on previous recruitment rates in the Butajira cohort study [5].

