**Methods:**

This is a cluster randomised trial set in a rural district in Ethiopia, with sub-district as the unit of randomisation. Participants will be recruited from an existing cohort of people with schizophrenia receiving treatment in primary care. Fifty-four sub-districts will be randomly allocated in a 1:1 ratio to facility-based care plus community-based rehabilitation (intervention arm) or facility-based care alone (control arm). Facility-based care consists of treatment by a nurse or health officer in primary care (antipsychotic medication, basic psychoeducation and follow-up) with referral to a psychiatric nurse-led outpatient clinic or psychiatric hospital when required. Trained community-based rehabilitation workers will deliver a manualised community-based rehabilitation intervention, with regular individual and group supervision. We aim to recruit 182 people with schizophrenia and their caregivers. Potential participants will be screened for eligibility, including enduring or disabling illness. Participants will be recruited after providing informed consent or, for participants without decision-making capacity, after the primary caregiver gives permission on behalf of the participant. The primary outcome is disability measured with the 36-item WHO Disability Assessment Schedule (WHODAS) version 2.0 at 12 months. The sample size will allow us to detect a 20 % difference in WHODAS 2.0 scores between treatment arms with 85 % power. Secondary outcomes include change in symptom severity, economic activity, physical restraint, discrimination and caregiver burden.

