### Primary hypothesis

People with schizophrenia who receive CBR in addition to FBC will experience greater reductions in disability compared to those who receive only FBC, to the order of 20 % absolute difference in WHODAS 2.0 score between groups, over a 12-month period.

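### The stated 85 % power does not belong to a 20 % absolute WHODAS difference: the protocol's own inputs give at least 99.4 % for 20 points, and 85 % for about 9 to 12 points

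*Protocol article*

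**What the plan says.** Three places in the protocol article state the effect.

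- Power calculation: "This sample size will allow us to detect a 20 % absolute difference in WHODAS 2.0 scores between treatment arms with 85 % power".
- Primary hypothesis: the benefit is expected "to the order of 20 % absolute difference in WHODAS 2.0 score between groups, over a 12-month period".
- Abstract, Methods: "The sample size will allow us to detect a 20 % difference in WHODAS 2.0 scores between treatment arms with 85 % power". Here the 20 % is not labelled absolute or relative.

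The inputs are also in the Power calculation section. On sample size, "the final sample size for analysis will be 140 participant dyads in 54 sub-districts (mean 2.6 participants/sub-district". On variance, k is given as the "coefficient of variation) of 0.14 and a within-cluster standard deviation (SD) of 16". The test level appears as "with 85 % power and 5 % significance", without saying one-sided or two-sided. Study design gives 27 sub-districts per arm. The assumed arm means are attributed to an Indian study of people with schizophrenia but are not printed.

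**The concern.** With a within-cluster SD of 16, a 20-point difference is 20/16 = 1.25 SDs. For an effect that large, 54 clusters and 140 analysed dyads look far too many to give only 85 % power. Either the power or the effect must be misstated.

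At stake is the benchmark against which the result will be read. The same 20 % is the primary hypothesis, so if the design was really sized for about 10 points, the published target is about twice what the trial was built to detect. A true 10-point benefit would then look like half the hypothesised effect.

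**Working it through.** **Inputs.** From Power calculation: 182 dyads recruited, 23 % attrition, 140 analysed, 54 clusters, m = 2.6 per cluster, within-cluster SD = 16, k = 0.14, 5 % significance, 85 % power. From Study design: c = 27 clusters per arm. Assumed: a two-sided test, a 0-100 score (the article does not give the range), and control means μ0 from 30 to 100, because the means are not printed.

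**The plan's own counts.** 182 × 0.77 = 140.1, and 140/54 = 2.59. These agree with the article, so the sample size is not in question.

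**Formula.** I used the standard (Hayes–Bennett) formula for means in an unmatched cluster trial with between-cluster coefficient of variation k:

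c = 1 + (1.96 + z_power)² × [2·SD²/m + k²(μ0² + μ1²)] / (μ0 − μ1)²

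Solved for power: Φ( |μ0 − μ1| / √V − 1.96 ), with V = [2·SD²/m + k²(μ0² + μ1²)] / (c − 1). The fixed terms are 2 × 256/2.6 = 196.92, k² = 0.0196 and c − 1 = 26.

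**A 20-point absolute difference.**

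- 50 v 30: V = (196.92 + 0.0196 × 3400)/26 = 263.56/26 = 10.14. Then 20/√10.14 = 6.28, and Φ(6.28 − 1.96) = 0.99999.
- 100 v 80: V = (196.92 + 0.0196 × 16400)/26 = 518.36/26 = 19.94. Then 20/√19.94 = 4.48, and Φ(4.48 − 1.96) = 0.994.

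Between these, power is 99.98 % at a control mean of 70, 99.93 % at 80 and 99.8 % at 90. It stays above 99.9 % up to about 83.

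**Clusters needed for 85 % power at 20 points.** With (1.96 + 1.036)² = 8.98, 50 v 30 needs 1 + 8.98 × 263.56/400 = 6.9 per arm. The figure is 7.7 at a control mean of 60 and 9.8 at 80, against 27 planned.

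**Robustness.** Dropping the one-cluster correction, or using a noncentral t with 52 df, barely changes the results. Taking m = 2.0 still leaves 98.9 % at a control mean of 100. A one-sided test only raises power. To bring 20 points down to 85 % at a control mean of 50, the SD would have to be about 37.7 or k about 0.53.

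**What 85 % power does correspond to.** Solving the same formula for the difference:

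| Control mean | Detectable difference at 85 % power | As % of control mean |
|---|---|---|
| 30 | 8.8 | 29 |
| 40 | 9.2 | 23 |
| 50 | 9.8 | 20 |
| 60 | 10.4 | 17 |
| 70 | 11.2 | 16 |
| 80 | 11.9 | 15 |

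**One reading that reproduces the stated figure.** If the 20 % is taken as relative, 85 % is reached at 48.5 v 38.8: V = (196.92 + 0.0196 × 3857.7)/26 = 10.48, 9.7/√10.48 = 3.00, and Φ(3.00 − 1.96) = 0.85. Under that reading, power is 64 % at a control mean of 35, 74 % at 40, 81 % at 45 and 86 % at 50.

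**The case against.** The strongest objection concerns what can be concluded beyond the mismatch.

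- **The intended effect is unknown.** A reader might infer that the sponsor used a 20 % relative difference of 9.7 points. The documents do not support that as a fact. The means are not printed, the source study is not available, and the table shows a continuum of mean and difference pairs that all give 85 %. The pair 48.5 v 38.8 appears only after 20 % relative has been assumed. The hypothesis speaks of greater reductions, so 20 percentage points between the arms' percentage reductions is also conceivable; at a baseline near 48 that again comes to about 9.7 points. This objection stands, and it limits what the fix can prescribe.
- **No test uses the 20 %.** The Data analysis section compares WHODAS scores between arms in a mixed-effects model, with no threshold. The number of dyads came from estimated availability, and recruitment is complete. So a reader who infers a wrong sample size, a wrong test or an inflated type I error goes too far. This also stands.
- **Precedent.** It is tempting to call 20 points implausible because the Background describes the Indian collaborative-care trial's effect as modest. That section gives no WHODAS figure, and it reports larger effects in rural areas with fewer resources. The argument cannot be made from these documents.
- **The abstract.** Leaving out the word absolute there is condensation and not a separate error. It still has to be aligned once the meaning is settled.

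None of this rescues the printed statement. No control mean from 30 to 100 brings a 20-point difference near 85 % power.

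**Conclusion.** The statement is wrong as written. On a 0-100 score with a two-sided 5 % test, the protocol's inputs give at least 99.4 % power for a 20-point absolute difference, not 85 %. Power of 85 % belongs to about 9 to 12 points for control means of 30 to 80, roughly half the stated effect. The mismatch does not depend on the unprinted means, but the exact replacement figure does.

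The consequence is a misstated target effect and power, carried into the primary hypothesis. If the 20 % proves to be relative, the unqualified 85 % also hides how strongly power depends on the control mean: it is 81 % at 45 and 74 % at 40. The inclusion criteria admit participants with a WHODAS score of 35 or more, or lower through other routes, so such means cannot be ruled out.

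**What to change.** Before unmasked analysis, the sponsor should:

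1. Confirm and print the control and intervention means used in the calculation.
2. Say whether the 20 % is absolute or relative and, if relative, to what.
3. Restate the target effect in WHODAS points so that it matches 85 % power. With the stated inputs this is about 9 to 12 points, depending on the control mean.
4. Use the same statement in the abstract, the Primary hypothesis and the Power calculation.
5. If the relative reading is confirmed, add a sentence saying that power falls when the control mean is lower.

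The cost is a correction of wording and one restated figure. It changes neither the sample size nor the analysis, and needs no extra participants. Making it before unmasking keeps the target from being reinterpreted in the light of the result.

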### Data management

All data collection and management will follow Good Clinical Practice (GCP) guidelines and SOPs. Each participant has a unique ID that will enable all data reported for each participant to be identified. Blinding will be maintained during data collection, entry, processing and primary data analysis. Data is collected on paper Patient Report Forms (PRF) and double entered onto electronic Case Report Forms on EpiData Entry Client (2.0.7.22). Data will be managed using EpiData Data Manager (2.0.8.56).

All databases will be password-protected and only accessible to authorised personnel. Data cleaning based on frequency distributions and logic checks will follow standard procedures with reference to source documents as required. The data system is designed to ensure that all data changes are documented and that there is no undocumented deletion of entered data, i.e. an audit trail will be in place. Systematic checks will be carried out to ensure that the audit trail is functioning correctly. Data and all appropriate documentation will be stored for a minimum of 5 years after the completion of the study, including the follow-up period.

### Data analysis

Data analysis will take place using Stata, version 13. The primary outcome analysis will be masked until the analysis is finalised and approved by all investigators. Adequate CBR will be defined as having received a minimum of ten home visits by a CBR worker. We will not define adequate treatment for the FBC arm a priori. Sociodemographic and clinical characteristics (including WHODAS 2.0 score) of eligible PRIME cohort participants who did and did not consent to RISE will be compared using chi-square tests and *t* tests. Loss-to-follow-up will be compared by treatment arm at 6 and 12 months to assess bias due to loss to follow-up. Of those who enrolled, descriptive summaries of sociodemographic and clinical characteristics, presented by treatment arm, will be produced for baseline data. CBR worker characteristics such as age, gender, education level and post-training competency will be described.

Endpoint data will be analysed under intention-to-treat assumptions. An individual-level analysis will be conducted using a multilevel, mixed-effects regression model to compare the WHODAS 2.0 score between treatment arms, accounting for clustering at sub-district and CBR worker levels. The WHODAS 2.0 distribution will determine the model used. If zero-inflation is detected, a zero-inflated negative binomial model will be considered [60]. Adjustment will be made for baseline WHODAS 2.0 score and covariates unbalanced at baseline. Logistic regression will be used to assess which baseline variables are associated with missing outcome data. Baseline variables that predict missing outcome will be included in the regression models as fixed covariates to meet the assumption that outcome data is missing at random. Multiple imputation methods will then be used for participants with missing outcome data.

Sensitivity analyses will include a complete case analysis and a complier average causal effect (CACE) analysis [61]. We will also assess whether there is a dose-response relationship between degree of adherence to CBR (i.e. number of sessions) and the primary outcome. A further analysis will be undertaken to understand which the active components of CBR are. Process data on which CBR components were received, and in what quantity, will be utilised. Potential correlations between different components will be taken into account.

Exploratory sub-group analyses by baseline symptom severity and antipsychotic medication adherence will be completed, although the study will not be powered to investigate such differential effects. A longitudinal analysis will be conducted using a random-effects model. Three levels (CBR worker, sub-district and individual) and two time points (6 and 12 months) will be included. Secondary and tertiary outcomes will be analysed using mixed-effects linear regression models or logistic regression depending on the data type.

### Cost-effectiveness analysis

Direct costs of the treatment will be estimated by deriving a monetary value for each component of the treatment based on actual costs, and applying these to each individual based on the process indicators, which reflect the actual uptake of the treatment. Other health care costs and other patient- or family-borne costs will be computed and compared at 6 and 12 months, and subsequently related to changes in disability and clinical symptoms. Incremental cost-effectiveness ratios will be calculated to illustrate the extra cost incurred (if any) to produce a unit improvement in the main outcome of disability-adjusted life years (DALYs) calculated from the 36-item WHODAS 2.0. In the event that dominance is not shown, i.e. the intervention is more effective but the costs are also more than the FBC group, incremental cost-effectiveness ratios will be computed, together with their confidence intervals (using bootstrapping techniques to overcome expected skewness of cost data). Cost-effectiveness acceptability curves will also be derived in order to show the probability of any cost-effective advantages for the FBC plus CBR group at a range of ‘willingness to pay’ threshold levels.

The results from the quantitative and qualitative work will be combined to give an overall assessment of the intervention effectiveness.

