### Secondary objectives

To evaluate the effectiveness of CBR plus FBC compared to FBC alone in reducing clinical symptoms, reducing relapse, increasing medication adherence, improving economic activity, reducing physical restraint, reducing discrimination, and improving nutritional status in people with schizophrenia.To evaluate the effectiveness of CBR plus FBC compared to FBC alone in reducing family burden, stigma and depression, and improving economic activity in caregivers of people with schizophreniaTo explore the acceptability and feasibility of CBR from the perspective of (1) those receiving the treatment, (2) their families, and (3) those delivering the treatment.To determine the cost-effectiveness of CBR plus FBC compared to FBC alone.To investigate the process through which CBR achieves its impact.

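### The planned bootstrap confidence interval on the cost-effectiveness ratio cannot be interpreted when the effect difference is not clearly above zero; incremental net benefit with an interval would serve better

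*Protocol article*

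**What the plan says.** Cost-effectiveness is a secondary objective: "To determine the cost-effectiveness of CBR plus FBC compared to FBC alone". The section 'Cost-effectiveness analysis' takes disability-adjusted life years derived from the WHODAS 2.0 as its main outcome and makes three statements that matter here.

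- It announces the ratio without condition: "Incremental cost-effectiveness ratios will be calculated to illustrate the extra cost incurred (if any) to produce a unit improvement".
- It then attaches a condition, "In the event that dominance is not shown, i.e. the intervention is more effective but the costs are also more than the FBC group". In that event ratios are to be computed "together with their confidence intervals (using bootstrapping techniques to overcome expected skewness of cost data".
- It adds a second summary: "Cost-effectiveness acceptability curves will also be derived in order to show the probability of any cost-effective advantages for the FBC plus CBR group". This is to be shown over a range of willingness-to-pay thresholds.

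The section gives no significance level, probability or margin for deciding that dominance has been shown. It does not name the type of bootstrap interval.

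**The concern.** The stated reason for the bootstrap is skewed costs. Skewness in the numerator is not the main difficulty with a ratio interval. The difficulty is a denominator, here the effect difference, whose sampling distribution may span zero.

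If CBR costs more, a replicate in which it also does worse gives a negative ratio. That is the worst outcome for CBR, but in numerical order it lies below every positive ratio. The same negative sign would arise from a replicate that is cheaper and better, which is the best outcome. The two cannot be told apart once only the ratio is kept. The lower limit can therefore fall below zero and look like a possible saving, while the upper limit stays finite although the data do not exclude no effect.

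At stake is how a stated secondary result reads when the disability effect is small or uncertain. The primary result is not touched.

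**Working it through.** **Plan's own figures.** The cost-effectiveness section gives none to reproduce. The only link to a size of effect is in 'Power calculation', where the WHODAS 2.0 comparison is planned "with 85 % power and 5 % significance". Taking 5% as two-sided, the powered effect in standard errors is 1.960 + 1.036 = 2.996, or about 3.0.

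**Assumptions, none of them in the documents.** Effect and cost differences are independent and normal, each measured in its own standard error (SE). The interval is the 95% percentile interval of the replicate ratios. The true cost difference is 4 to 10 SE. The economic outcome has no stated power, so z = 3.0 is borrowed from the WHODAS 2.0 score.

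**When the lower limit is negative.** If cost is clearly positive in almost every replicate, a ratio is negative exactly when the replicate's effect is at or below zero. With an observed effect of z_obs SE, that share of replicates is Φ(−z_obs). The lower 2.5% point is negative when this share exceeds 2.5%, that is, when z_obs < 1.96. So the interval loses its meaning exactly when the effect is not significant at the two-sided 5% level. For example, at z_obs = 1 the share is Φ(−1) = 16%.

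**How often this occurs.** Among trials with a positive observed effect and true effect z, the share is

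[Φ(1.96 − z) − Φ(−z)] / Φ(z)

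- z = 0: (0.975 − 0.500) / 0.500 = 95%
- z = 1.5: (0.677 − 0.067) / 0.933 = 65%
- z = 3.0: (0.149 − 0.001) / 0.999 = 15%

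**Simulation check.** Drawing trials, keeping those with CBR more effective and more costly, and bootstrapping the ratio gave:

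| True effect | Formula | Simulated, cost difference 4 to 10 SE |
|---|---|---|
| 0 | 95% | about 95% |
| 1.5 SE | 65% | about 65% |
| 3.0 SE | 15% | about 15–17% |

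Runs with fewer trials and replicates, at 4 SE, gave 94%, 65% and 18%, which is within simulation error. The small excess over the formula at 4 SE comes from trials whose observed cost difference is itself not far from zero. With no effect, on average 25% of replicates in this branch had an effect at or below zero.

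**Coverage.** The interval contained the true ratio in about 97% of trials in this branch at z = 1.5 and at z = 3.0. The fault is therefore not under-coverage. It is that the limits cannot be read as a range of ICERs when the lower one is negative for this reason.

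**Acceptability curve, for comparison.** With no effect and a cost difference of 4 SE, the curve rises from 0.00 at zero willingness to pay to 0.50 at very high values. It exceeds 0.95 in 0% to 4.9% of trials, depending on the threshold. The curve does not mislead in the setting where the ratio interval does.

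**The case against.** The strongest reply has four parts.

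1. *No dominance rule is written.* A reader might infer from the condition that dominance is read off the signs of two point estimates, and that with no effect FBC would be called dominant in about half of trials. The documents do not support that. They do not say how dominance is shown, never speak of declaring FBC dominant, and announce ratios without condition earlier in the section. The figure of one half also needs a clearly positive cost difference. With no effect, the share of trials in which CBR is costlier and less effective is 0.5 × Φ(cost difference in SE): 25% at 0, 42% at 1, 49% at 2 and 50% at 4. The plan gives no cost figures and writes of extra cost only if there is any. This part stands, and no claim about a dominance verdict is made here.

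2. *The acceptability curves already cover all four quadrants.* This stands as a reason to rate the point low. But the curves are planned in addition to the interval, so the interval would still be reported.

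3. *The percentile method is assumed, and an article may leave interval details to the analysis plan.* That is fair as to detail, and the percentages depend on it. What the article does fix is a confidence interval on the ratio. Reordering the replicates would cure the sorting, but when the effect may be zero the ratio still has no finite upper bound that the data support.

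4. *Cost differences are reported too, so a negative limit need not be read as a saving.* Partly so. A careful reader would notice, but an interval that must be corrected from another table is a poor summary.

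**Conclusion.** The point holds in a limited form. The protocol article prescribes an interval on a ratio that becomes uninterpretable when the effect difference is not significantly above zero. Under the stated assumptions this affects about 95% of such intervals with no effect, about 65% at half the powered effect, and about 15–17% at the powered effect, where coverage is about 97% and most intervals behave. A smaller cost difference, correlated or skewed estimates, or another bootstrap interval would change these percentages.

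The section is also unclear about what will be reported outside the quadrant it describes, since one sentence promises ratios in general and the next ties them to a condition. Because the objective is secondary and acceptability curves are already planned, this is a cheap improvement of minor priority.

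**What to change.** Replace the confidence interval on the ICER by incremental net monetary benefit, λ × (effect difference) − (cost difference), with a 95% interval at each willingness-to-pay threshold λ already intended for the acceptability curves. Report it whatever quadrant the point estimates fall in. It is a difference and not a ratio, so it is well defined when the effect is near zero.

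Take the interval from bootstrap replicates that respect the sub-district clusters, for example by resampling sub-districts within arm, because the sub-district is the unit of randomisation. Give the ICER as a point estimate only, beside the separate cost and effect differences, the cost-effectiveness plane and the acceptability curve from the same replicates. Delete the condition on dominance, or state plainly that it does not govern what is reported.

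The cost is a change of wording, since the curves need joint cost and effect replicates in any case. The downside is that results are shown over a range of thresholds instead of as one ratio interval.
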